# STATISTICAL CONSIDERATIONS

## Study Design/Endpoints

The primary objective of this trial is to determine the MTD or recommended Phase 2 dose (RP2D) of Artesunate. The MTD will be determined using a modified 3 + 3 design, in which the MTD is defined as the highest dose level tested at which ≤20% patients experience dose limiting toxicity (DLT). The 3 + 3 dose escalation will consist of 6 dose levels in combination with variation in dosing schedules the single agent Artesunate. In addition, if DLT’s are identified at any dose, there are possible intermediate dose de-escalation steps allowed (i.e. to have only one administration at a particular dose) An expansion cohort will occur at MTD. Once MTD is found, then secondary outcomes will be evaluated. There is a 1-week washout period before advancing to the next Artesunate dose level.

| **Dose Escalation Design** | | | | |
| --- | --- | --- | --- | --- |
| **Cohort** | **Dose (mg)** | **Number of Treatment Cycles** | **Designated Weeks of Artesunate Administration** | **Number of patients** |
| **I** | 200 | 2 | 0, 2 | 3 |
| **II** | 200 | 3 | 0, 2, 4 | 3 |
| **III** | 400 | 2 | 0, 2 | 3 |
| **IV** | 400 | 3 | 0, 2, 4 | 3 |
| **V** | 600 | 2 | 0, 2 | 3 |
| **VI** | 600 | 3 | 0, 2, 4 | 3 |

More specifically:

This is a modified 3 + 3 design. Based on previous studies of rectally administered Artesunate for the treatment of malaria, the safety profile demonstrates a low probability of dose limiting toxicity in children, as well as adults. The first cohort will consist of 3 patients who receive the initial dose of a 200-mg suppository administered in cycles of 5 daily doses at weeks 0 and 2. If none of the three patients in a cohort experiences a dose-limiting toxicity, another three patients will be treated at the next higher dose level. If 1 out of 3 patients experiences dose-limiting toxicity, then the next 3 patients will be treated at the same dose level. If 2 out of 6 patients experience a DLT, then de-escalation to the next lower level will occur. The modification of the 3 + 3 design consists of the extra de-escalation steps as noted on the left of the diagram pictured below.

If any dose has 2 (or more) DLTs then the MTD will be the dose that is below that dose that has 1 or less DLTs out of 6 patients. Once the MTD is identified then additional patients will be added to this cohort to allow a total of 12 patients.

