## Definition of Dose-Limiting Toxicity

A dose-limiting toxicity (DLT) is defined as any drug-related Grade 2 (moderate; minimal, local, or noninvasive intervention indicated; limiting age appropriate instrumental ADL) or greater drug-related toxicities in any organ system (or Grade 3 or greater toxicities–severe or medically significant but not immediately life-threatening; hospitalization or prolongation of hospitalization indicated; disabling; limiting self care ADL**) in any organ system (including gastrointestinal, dermatologic, and neurologic), as delineated in Common Terminology Criteria for Adverse Events v4.0 (CTCAE).

This above definition of dose-limiting toxicity applies to the drug that is being studied—the artesunate suppository. Post-procedural complications related to the HRA procedure are not dose limiting.

The dose limiting toxicity determining period for the study will extend to 1 week after the last cycle of artesunate suppository. Thus, for the 2 cycles, the DLT determining period will extend to 3 weeks; for 3 cycles, it will extend to 5 weeks.

Beyond the DLT determining period, if patients in a specific cohort have complete resolution of their high-grade dysplastic lesions, then the plan will be to stop at this dosing cycle and frequency and move into the 12-patient expansion cohort.

Management and dose modifications associated with the above adverse events are outlined in Section 6.

Dose escalation will proceed within each cohort according to the modified 3+ 3 design with de-escalation schema and an expansion cohort at MTD. Dose-limiting toxicity (DLT) is defined as above.

The specific details are as follows,

The 3 + 3 dose escalation will consist of 6 dose levels in combination with variation in dosing schedules the single agent Artesunate, with additional de-escalation steps. An expansion cohort of 12 patients will be included at the MTD. Once MTD is found, then secondary outcomes will be evaluated. In MTD expanded patient cohort, anal intraepithelial neoplasia (AIN) regression from AIN 2/3 to low-grade anal intraepithelial neoplasia (AIN 1) or no residual AIN will be assessed through subsequent HRA evaluation. Cytology specimens will be tested through quantitative PCR for HPV viral load during initial and subsequent HRA evaluations. A tissue bank will be created for future studies.

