# ADVERSE EVENTS: LIST AND REPORTING REQUIREMENTS

Because this is a pilot study evaluating tolerability of a new intra-anal treatment, the stopping rule for safety is the presence of drug-related Grade 3 toxicity in any organ system (including gastrointestinal, dermatologic, and neurologic toxicities) delineated in CTCAEv4.0. In the event of two identical unexpected treatment-related Grade 2 or greater toxicities in any organ system ( or other Grade 3 or greater toxicities), accrual will be suspended pending further review.

Subjects who become pregnant during study will be required to discontinue drug. Although not considered an adverse event, pregnancy will be reported in the same way. Whenever possible, a pregnancy should be followed to term, and the status of mother and child reported. The Pregnancy Notification form will be sent to the principal investigator ([name]) within 48 hours of discovery. Whenever possible, the Follow-up Pregnancy Outcome Form will be filled after delivery.

Finally, if there is evidence of disease progression at the interval visit regardless whether the progression may or may not be associated with Artesunate, patients will undergo HRA biopsy and ablation at that point.

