## AE Reporting

Expected Aes will be reported to the JHM IRB and reviewed at the time of the annual review. The University of Wisconsin team will enter all expected adverse events into the REDCap database within 2 weeks. The JHU team will compile all Adverse Events from both institutions for the annual review by the JHM IRB. Any drug-related SAEs or multiple occurrences of an AE determined to be an unanticipated problem will be reported by both institutions to the Johns Hopkins Institutional Review Board and the Johns Hopkins Cancer Center Clinical Research Committee. Drug-related SAE’s will be reported to all regulatory agencies by the study PI ([name]) within 7 working days. Any drug-related SAEs reported by a study participant at the University of Wisconsin will be reported to the JHU PI within 3 business days, in order to allow sufficient time for the expedited reporting by the JHU PI. Unanticipated or unexpected AE is defined as any AE not listed in available sources including the labeling, the Investigator’s Brochure, or this protocol.

PHARMACEUTICAL INFORMATION

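### If 2 or more patients in a failed two-cycle cohort had DLTs from cycle 1, section 14.1 still lets the one-cycle step, the same treatment as that cycle 1, be opened and named MTD

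*Protocol*

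**What the plan says.** Section 14.1 gives the trigger as "If 2 out of 6 patients experience a DLT, then de-escalation to the next lower level will occur", and adds that there are "possible intermediate dose de-escalation steps allowed (i.e. to have only one administration at a particular dose". The surviving diagram text shows three such steps: 200, 400 and 600 mg, five daily doses, one cycle at week 0. Cohorts I, III and V give the same five doses at week 0 and repeat them at week 2.

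Once a dose has 2 or more DLTs, "the MTD will be the dose that is below that dose that has 1 or less DLTs out of 6 patients". The MTD is defined as the "highest dose level tested at which ≤20% patients experience dose limiting toxicity (DLT").

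On counting, section 5.2 states: "The dose limiting toxicity determining period for the study will extend to 1 week after the last cycle of artesunate suppository". That makes 3 weeks for two cycles and 5 weeks for three. No window is stated for one cycle. A DLT begins at drug-related Grade 2.

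Two study-wide brakes stand in section 6: "the stopping rule for safety is the presence of drug-related Grade 3 toxicity in any organ system", and suspension of accrual after "two identical unexpected treatment-related Grade 2 or greater toxicities in any organ system". Section 6.4 adds: "Unanticipated or unexpected AE is defined as any AE not listed in available sources including the labeling", and the listed sources also include the Investigator's Brochure and the protocol itself.

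**The concern.** A one-cycle step is a sensible retreat when toxicity appears in cycle 2 or builds up with repeated dosing. It is no retreat when the DLTs came from cycle 1, because the new patients then receive the exposure that produced them. The trigger counts patients with a DLT over the whole period and ignores when each DLT began, so the plan treats the two situations alike.

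Up to 6 further patients could be given a regimen that has already produced 2 or more DLTs. The MTD, which is the primary endpoint, and the group filled to 12 at that level could rest on a regimen whose first-cycle record in this trial is above the protocol's own limit.

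**Working it through.** **Reading used.** The diagram's arrows are not visible. Placing the one-cycle steps below cohorts I, III and V rests on the box text, on the wording of 14.1 about a single administration at a given dose, and on 14.2, which speaks of de-escalating the frequency of cycles. The stated sample size fits three such steps: 6 levels × 6 = 36; 3 steps × 6 = 18; 6 more to bring the MTD level from 6 to 12; 36 + 18 + 6 = 60. This reproduces 36 and 60, but the split of the extra 24 is inferred, since the protocol does not itemise it.

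**Does section 6 close the path?** Only in part. The Synopsis lists dizziness, nausea, emesis and abdominal pain as known effects, so they are not unexpected under 6.4. Two Grade 2 DLTs of those kinds, or two differing Grade 2 DLTs, fail the cohort without triggering either brake.

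**Pooled first-cycle data when the step passes:**

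| Cycle-1 DLTs in two-cycle cohort | One-cycle step | Pooled |
|---|---|---|
| 2/6 | 0/6 | 2/12 = 17% |
| 2/3 | 0/6 | 2/9 = 22% |
| 2/6 | 1/6 | 3/12 = 25% |
| 3/6 | 0/6 | 3/12 = 25% |
| 2/3 | 1/6 | 3/9 = 33% |

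Rarer, worse cohorts pool higher, for example 3/3 then 1/6 = 4/9 = 44%.

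**How often.** The protocol gives no DLT rates, so these are assumptions: q = first-cycle rate; r = second-cycle rate in patients without a cycle-1 DLT. Cohort V takes 3 patients, 3 more if exactly 1 has a DLT, and fails at 2 or more. The 600 mg one-cycle step is filled to 6 and passes at 1 or fewer.

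- J = P(cohort V fails with 2 or more cycle-1 DLTs). For r = 0, J = [1 − (1−q)³ − 3q(1−q)²] + 3q(1−q)²[1 − (1−q)³]. For r > 0, each patient has a cycle-1 DLT (q), a cycle-2 DLT only ((1−q)r) or none, and J is enumerated exactly over the two stages.
- P = P(step passes) = (1−q)⁶ + 6q(1−q)⁵.
- Worked at q = 0.30, r = 0: J = 0.216 + 0.441 × 0.657 = 0.506; P = 0.118 + 0.303 = 0.420; J × P = 0.212. Removing 2/6 then 0/6 (0.441² × 0.118 = 0.023) leaves 0.190.

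| q | J (r=0 / r=q) | P | J × P (r=0 / r=q) | with pooled rate above 20% |
|---|---|---|---|---|
| 0.10 | 0.094 / 0.086 | 0.886 | 0.083 / 0.076 | not harm |
| 0.20 | 0.291 / 0.244 | 0.655 | 0.191 / 0.160 | not harm |
| 0.25 | 0.400 / 0.321 | 0.534 | 0.214 / 0.172 | 0.182 / 0.149 |
| 0.30 | 0.506 / 0.391 | 0.420 | 0.212 / 0.164 | 0.190 / 0.150 |
| 0.40 | 0.691 / 0.507 | 0.233 | 0.161 / 0.118 | 0.152 / 0.114 |

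At q = r = 0.05, J × P = 0.025. With mostly late toxicity (q = 0.10, r = 0.30) it is 0.061, and only 0.069 of the 0.640 failures (11%) have 2 or more cycle-1 DLTs. Rows marked as not harm have a true rate within the 20% limit.

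**The case against.** **The diagram is not visible.** It might settle the order of levels, and the next lower level after V could be IV. This stands as a limit: the point is conditional on the reading. But 14.1 expressly allows the one-cycle steps, and no visible text makes them depend on cycle of onset.

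**The steps are optional and overseen.** The wording is permissive. Weekly review of case report forms, staff safety meetings and monitoring committees surround the decision. A reader might infer that the protocol obliges the team to re-test the failed exposure, and that is not supported. Oversight still does not supply the missing bar.

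**The 20% definition might already exclude these cases.** It would if earlier first-cycle patients counted toward the one-cycle regimen. Nothing says they do, and the selection rule asks only for 1 or fewer of 6.

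**Pooled rates are weak estimates.** They include a cohort selected for having failed, and they are imprecise: the exact 95% interval is 3–60% for 2/9 and 5–57% for 3/12. This is correct. The pooled figures show an inconsistency between decision rules and do not prove that the true rate exceeds 20%.

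**The size is easily overstated.** A reader might take 12–22%, the chance of any one-cycle pass after 2 or more cycle-1 DLTs at q of 25–40%. That range includes 2/6 then 0/6, which is within the limit. The relevant range is 11–19%. It is an upper bound because section 6 halts are not removed, and it is conditional on reaching cohort V. Section 14.1 itself expects DLTs to be rare.

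**Same treatment does not mean same ascertainment.** The 3- and 5-week windows equal the last cycle's start plus 1 week (2 + 1, 4 + 1), which implies 0 + 1 = 1 week for one cycle. A DLT beginning in days 8–14 counts in the two-cycle cohort but might not count at the step. The fix has to define that window.

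**Conclusion.** The point holds in a conditional form and is worth correcting. As written, 14.1 and 5.2 allow a one-cycle regimen that has already met the failure criterion of 2 or more DLTs to be opened in new patients and named MTD on 1 or fewer of 6. This needs three conditions: the one-cycle steps belong to cohorts I, III and V; 2 or more patients' DLTs came from cycle 1; and section 6 did not halt the trial.

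In the combinations with 2 or 3 DLTs in total, the pooled first-cycle rate is 22–33%, except 17% for 2/6 then 0/6. At assumed first-cycle rates of 25–40%, with r from 0 to q, a pass with a pooled rate above 20% occurs in at most 11–19% of trials reaching cohort V. At 5–10%, a one-cycle pass after 2 or more cycle-1 DLTs occurs in 2.5–8% and does no harm, because the regimen is then acceptable.

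A reader might infer that the one-cycle steps are unsound in general. The documents do not support that: for late or cumulative toxicity they are a real reduction in exposure. Confidence is medium, because the arrows are unseen and every DLT rate is assumed.

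**What to change.** In 14.1, repeated in 5.2:

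1. State the DLT window for a one-cycle regimen, for example up to the planned start of cycle 2, or the one week that 5.2 implies.
2. Add: *After cohort I, III or V fails, the one-cycle step at that dose is opened only if fewer than 2 patients in that cohort had a DLT with onset within the one-cycle DLT window and before any cycle-2 dose. Otherwise the one-cycle step is taken as failed and de-escalation goes to the next lower daily dose (IV after V, II after III). After cohort I, accrual is suspended for safety review.*

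The cost is a few sentences and no extra patients. Onset by cycle is already captured by the per-cycle symptom diary (Appendix B) and the call after each cycle (8.2).

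The downside is that an acceptable one-cycle regimen is sometimes skipped. Per trial reaching V, this happens in about 24–29% at a true first-cycle rate of 20% (in 16–19% it would have passed) and in 7–9% at a true rate of 10%. The rule also forecloses 2/6 then 0/6. The plan already accepts this loss at every other level that reaches 2 DLTs.

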**Cohort I**:

**200 mg** x 5 daily doses/cycle.

**2 cycles** administered at weeks 0, 2

**Cohort III**:

**400 mg** x 5 daily doses/cycle.

**2 cycles** administered at weeks 0, 2

**Cohort IV**:

**400 mg** x 5 daily doses/cycle.

**3 cycles** administered at weeks 0, 2, 4

**De-escalate** to **200 mg** x 5 daily doses/cycle.

**1 cycle** administered at week 0

**De-escalate** to **400 mg** x 5 daily doses/cycle.

**1 cycle** administered at week 0

**Cohort II**:

**200 mg** x 5 daily doses/cycle.

**3 cycles** administered at weeks 0, 2, 4

**Cohort VI**:

**600 mg** x 5 daily doses/cycle.

**3 cycles** administered at weeks 0, 2, 4

**Cohort V**:

**600 mg** x 5 daily doses/cycle.

**2 cycles** administered at weeks 0, 2

**De-escalate** to **600 mg** x 5 daily doses/cycle.

**1 cycle** administered at week 0

**At MTD, expansion cohort**, n = 12.

De-escalate

De-escalate

De-escalate

De-escalate

## Sample Size/Accrual Rate

A total of up to 60 patients (36 expected from the 3+3 design, with extra allowable with the modified escalation schema to account for de-escalation in cycle frequency) will be accrued to the study. It is expected that 6 evaluable patients will be enrolled per month.

## Analysis of Primary and Secondary Endpoints

- - 1. Analysis of safety endpoints

The NCI common terminology criteria for adverse events (AE) (CTCAE 4.0) will be used to evaluate toxicity. We will consider a toxicity to be an adverse event that is possibly, probably or definitely related to treatment. The maximum grade of toxicity for each category of interest will be recorded for each patient, and the summary results will be tabulated by category, grade, and dose level. Serious (≥ Grade 3) toxicities will be described on a patient-by-patient basis and will include any relevant baseline data.

Once the MTD (or RP2D) is found, then secondary outcomes will be evaluated based on MTD.

- - 1. Analysis of secondary efficacy endpoints

Regression of AIN 2/3 to either AIN 1 or the absence of AIN will be used as dichotomous variables and the proportion of patients with the characteristics and the corresponding 95% confidence intervals will be calculated.

HPV viral genotype will be collected longitudinally over time as a qualitative measure.

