# OBJECTIVES

## Primary Objectives

- - 1. To evaluate the safety and tolerability of intra-anal administration of Artesunate, administered via suppository with 3 different schedules, in patients with high-grade anal intraepithelial neoplasia (AIN 2/3).]

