## Definition of a Serious Adverse Event

A serious adverse event or reaction is any untoward medical occurrence that at any dose:

- - - results in death
    - is life-threatening (an event in which the subject is at risk of death at the time of the event; it does not refer to an event which hypothetically might have caused death if it were more serious)
    - requires inpatient hospitalization or prolongation of existing hospitalization
    - results in persistent or significant disability or incapacity
    - is a birth defect/congenital anomaly

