## Expedited Adverse Event Reporting

The severity of each adverse event must be assessed using the NCI Common Terminology Criteria for Adverse Events, v4.0 (CTCAE 4.0).

All adverse events that occur from the time of study drug administration through 30 days after the final treatment will be recorded. Duration, severity, treatments administered and outcome for each adverse event will be recorded on the CRF (case report form) for the following visit. Drug related adverse events will be followed until resolved, until no further improvement is expected, until a non-study antitumor therapy is initiated, or for 30 days after last study treatment, whichever comes first (with the exception of neuropathy, which must be followed until resolution to toxicity grade 1 or until stable for 60 days).

Adverse events beginning 30 days after the last treatment that the investigator considers to be related to study treatment will be reported to the appropriate contact person at any time such events occur.

Conditions that were present at the study start and that worsen during the study should be reported as beginning on the date the event worsened, not the date it began pre-study. Event text may include the word “worsened” or “exacerbated.”

Conditions which were recorded as “intermittent” at the study start which occur during the study must be reported if they are more frequent or of greater severity.

**Phase 1 and Early Phase 2 Studies: Expedited Reporting Requirements for Adverse Events that Occur on Studies under an IND/IDE within 30 Days of the Last Administration of the Investigational Agent/Intervention** 1, 2

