| **FDA REPORTING REQUIREMENTS FOR SERIOUS ADVERSE EVENTS (21 CFR Part 312)**  **NOTE:** Investigators **MUST** immediately report to the sponsor (NCI) **ANY** Serious Adverse Events, whether or not they are considered related to the investigational agent(s)/intervention (21 CFR 312.64)  An adverse event is considered serious if it results in **ANY** of the following outcomes:   1. Death 2. A life-threatening adverse event 3. An adverse event that results in inpatient hospitalization or prolongation of existing hospitalization for ≥ 24 hours 4. A persistent or significant incapacity or substantial disruption of the ability to conduct normal life functions 5. A congenital anomaly/birth defect. 6. Important Medical Events (IME) that may not result in death, be life threatening, or require hospitalization may be considered serious when, based upon medical judgment, they may jeopardize the patient or subject and may require medical or surgical intervention to prevent one of the outcomes listed in this definition. (FDA, 21 CFR 312.32; ICH E2A and ICH E6). | | |
| --- | --- | --- |
| **ALL SERIOUS** adverse events that meet the above criteria MUST be immediately reported to the NCI via electronic submission within the timeframes detailed in the table below. | | |
| **Hospitalization** | **Grade 3-5**  **Timeframes** |  |
| Resulting in Hospitalization  ≥ 24 hrs | 24-Hour 5 Calendar Days |  |
| Not resulting in Hospitalization  ≥ 24 hrs |  |
| **NOTE:** Protocol specific exceptions to expedited reporting of serious adverse events are found in the Specific Protocol Exceptions to Expedited Reporting (SPEER) portion of the CAEPR.  **Expedited AE reporting timelines are defined as:**   - “24-Hour; 5 Calendar Days” – The AE must initially be submitted electronically within 24 hours of learning of the AE, followed by a complete expedited report within 5 calendar days of the initial 24-hour report. | | |
| 1Serious adverse events that occur more than 30 days after the last administration of investigational agent/intervention and have an attribution of possible, probable, or definite require reporting as follows:  **Expedited 24-hour notification followed by complete report within 5 calendar days for:**   - All Grade 3, 4, and Grade 5 Aes | | |

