## Dosage and Administration

the first dosing visit (week 0) will be an in-person visit, in which tthe study physician or nurse will administer the first of five daily intra-anal suppositories for each enrolled subject at the study site. The subjects will be trained by the physician or nurse on the insertion of artesunate suppositories transanally during that visit, and instructed to administer four subsequent daily doses at home. All subsequent dosing visits (weeks 2 and 4) will be performed as telemedicine visits. For telemedicine visits, the physicians will review the symptom diaries and patients will be instructed about suppository administration over the phone. Within 5 days of the last day of the cycle(s), patients will receive a telephone call to assess for any AE. If patients do not experience any symptoms or AEs after suppository administration, then the subsequent dosing visits will be telemedicine visits. However, if patients experience AEs, then the subsequent dosing visits will be in-person visits, at which time the physician will perform an anoscopy.

The first 3 study subjects (healthy volunteers with AIN2/3) will receive five (5) daily suppositories that contain 200 mg Artesunate for a total of 2 cycles at weeks 0 and 2. The 200 mg dose (or ≤ 4 mg/kg for subjects weighing 50 kg at minimum) is considerably lower than that used when the anal suppository is intended to deliver a systemic dose of drug for malaria – the 10 mg/kg (50 mg) suppository is recommended by WHO for pediatric care. If no severe local irritation or systemic toxicities are observed in the first 3 patients at 200 mg, the dosage will escalate to 3 cycles of 200 mg per day. Doses of escalation will be 200 mg, 400 mg, and 600 mg. Suppositories will be administered daily for 5 days. Five days constitutes 1 cycle. Up to 3 cycles will be administered at Weeks 0, 2, and 4. Please see section 5 for dose escalation schema.

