## Assessment of Subject Compliance with Self Administration of Artesunate Suppositories

Eligible patients will have clinic or telemedicine visits scheduled at weeks 0, 2, and 4 for a urine pregnancy test (if female) and dosing. Once documentation of a negative pregnancy test is obtained (women of childbearing potential only), the patient will receive 5 doses of Artesunate for the respective treatment cycle. They will receive instructions on how to apply the suppositories and will apply the first dose of Artesunate during this visit. At each dosing visit, the study team will confirm contact information where they can be reached the following week. At dosing visits 2 and 3, if done in person, patients will have an anoscopy to assess the dentate line, and document any adverse events. For telemedicine visits, the investigator and/or study coordinator will review the Symptom Diary with the patient anddocument AEs. The Investigator will grade and determine causality to the study medication. Patients will have an in-person additional anoscopy and HPV genotyping at week 6 (+/- 1 week).

Patients will be monitored throughout the study for both known potential risks and for unexpected risks. During office visits, patients will be monitored specifically for any signs of:

- - - Symptoms of itching, burning, pain, warmth, or tenesmus
    - Signs of skin breakdown including erythema, blistering, desquamation, ulceration or bleeding
    - Neurologic symptoms
    - Unexpected adverse events

Subjects will be given diary cards to record local and general signs and symptoms most likely to occur between office visits. The diary cards will be collected, signs and symptoms verified, and inserted into the CRF at each subsequent visit.

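### Section 14.3 confines its safety table and patient descriptions to events judged related, so AEs and SAEs judged unlikely or unrelated appear in neither (minor)

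*Protocol*

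**What the plan says.** The primary objective (section 1.1) is "To evaluate the safety and tolerability of intra-anal administration of Artesunate".

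Section 14.3 defines the unit of its safety analysis: "We will consider a toxicity to be an adverse event that is possibly, probably or definitely related to treatment". It then names two outputs, both in terms of that unit. The first is a table of each patient's maximum grade of toxicity, by category, grade and dose level. The second is a set of individual accounts: "Serious (≥ Grade 3) toxicities will be described on a patient-by-patient basis and will include any relevant baseline data".

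Collection is wider than analysis. Section 6.3 states: "All adverse events that occur from the time of study drug administration through 30 days after the final treatment will be recorded". Its reporting table requires SAEs to be reported "whether or not they are considered related to the investigational agent(s)/intervention". Section 6.4 has all AEs from both sites compiled for the annual IRB review.

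On attribution, section 6.2 gives five categories, from definite to unrelated, and section 6.11 says who decides: "The Investigator will grade and determine causality to the study medication".

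On seriousness, section 6.1 begins "A serious adverse event or reaction is any untoward medical occurrence that at any dose" and goes on to list outcomes such as death, hospitalization and disability. It sets no CTCAE grade.

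**The concern.** In a small dose-escalation trial without a control arm, the attribution of a single event rests on judgement. The usual protection is to show all AEs by dose, with the related ones as a subset, so that a reader can see whether events judged unrelated also become more frequent as dose rises. The outputs in 14.3 do not allow that check.

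The local setting gives the point some substance. Anal brushing and anoscopy act on the same tissue as the suppository, so pain, bleeding or irritation could be put down to a procedure. Patients who report AEs also have more procedures, because section 6.9 says: "However, if patients experience AEs, then the subsequent dosing visits will be in-person visits, at which time the physician will perform an anoscopy".

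A second, smaller matter is wording. Section 14.3 uses 'serious' for a severity grade, whereas sections 6.1 and 6.3 define it by outcome.

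**Working it through.** The protocol states no figure to reproduce. The check is mainly a comparison of sections.

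**1. Which attribution categories reach the 14.3 outputs** (categories from section 6.2)

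| Attribution | Recorded (6.3) | 14.3 table | 14.3 patient descriptions |
|---|---|---|---|
| Definite, probable, possible | yes | yes | if Grade 3 or higher |
| Unlikely, unrelated | yes | no | no |

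Three of the five categories enter and two do not. The exclusion also applies to an SAE judged unlikely or unrelated.

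**2. Whether another section supplies an all-attribution analysis**

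Section 10.1 tabulates 'all toxicities' from the CRFs. That is the term 14.3 defines as related events, so 10.1 is at best ambiguous. Sections 6.3 and 6.4 concern reporting and oversight and give no analysis by dose level. No section specifies a by-dose table of AEs regardless of attribution.

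**3. Procedures at the same site during AE recording**

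Inputs: five daily doses per cycle, starting at weeks 0, 2 and 4 (section 5.1); one-cycle de-escalation levels (sections 5.1 and 14.1); recording to 30 days after final treatment (6.3); week 6 visit within one week either side (8.2); procedures from Appendix A. Day 0 is the first dose, and visits are on nominal days.

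End of recording = first day of last cycle + 4 + 30.

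| Schedule | Last dose | Recording ends | Week 0 brushing (day 0) | Week 6 brushing and anoscopy (day 42) |
|---|---|---|---|---|
| 1 cycle | day 4 | day 34 | inside | outside, even at the earliest day, 35 |
| 2 cycles | 14 + 4 = day 18 | day 48 | inside | inside |
| 3 cycles | 28 + 4 = day 32 | day 62 | inside | inside |

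With 2 or 3 cycles, brushing falls inside at two visits and anoscopy at one. If weeks 2 and 4 (days 14 and 28) are in person, these become four and three. The earliest post-dose HRA is 16 × 7 − 14 = day 98, outside every recording period.

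**4. Size**

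The documents give neither a local event rate nor a share judged unrelated, so the following only shows how the answer depends on assumed values. Let p be the share of patients with a given local event and m the share of those events judged unlikely or unrelated. With independent patients and the total of 12 at the MTD given in section 14.1:

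P(table shows no such event) = (1 − p(1 − m))^12

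| p | m = 0 (all-AE table) | m = 5% | m = 25% | m = 50% |
|---|---|---|---|---|
| 10% | 0.900^12 = 28% | 0.905^12 = 30% | 0.925^12 = 39% | 0.950^12 = 54% |
| 20% | 0.800^12 = 7% | 0.810^12 = 8% | 0.850^12 = 14% | 0.900^12 = 28% |
| 30% | 0.700^12 = 1% | 0.715^12 = 2% | 0.775^12 = 5% | 0.850^12 = 14% |

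At m = 5% the two tables are almost the same. Nothing in the protocol supports the larger values of m over the smaller ones.

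**5. The word 'serious'**

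Under 14.3, a related Grade 3 event that meets no criterion in 6.1 is called serious, and a related SAE below Grade 3 gets no individual description, although it stays in the table.

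**The case against.** The strongest reply is that this is an omission and not an error. Section 14.3 says how toxicities are tabulated and does not say that nothing else will be. All-AE tables and SAE listings often come from the SAP, which is not shown. This stands in part: an SAP could add both outputs. But 14.3 is not silent. It fixes a restrictive definition and builds both of its safety outputs on it.

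A second reply is that section 10.1 already covers all events. Sections 5.2 and 6 speak of drug-related or treatment-related toxicities, and those qualifiers would be redundant if the bare word always meant related. That makes 10.1 ambiguous, but it does not make it an all-attribution analysis by dose.

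A third reply is that the procedural route to misattribution is weak, and much of this stands. The week 6 procedures come 24 days after the last dose with 2 cycles (42 − 18) and 10 days after with 3 (42 − 32), and they cannot explain earlier symptoms. The table keeps each patient's maximum grade per category. Once a related event is counted, a later one matters only if it is of higher grade or in another category. Some events put down to a procedure will be correctly so.

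A fourth reply is that 'serious' is explained in place by its grade threshold, so it can hardly be misapplied. Section 5.2 itself places hospitalization and disability at Grade 3, which leaves few related SAEs below that grade. This stands, and the point is one of terminology.

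A reader might infer more: that unrelated SAEs go unreported, that the MTD could be biased, or that every patient has these procedures during recording. The documents support none of these. SAEs are reported whether or not related. The MTD rests on the DLT definition in section 5.2 and the counting rule in 14.1. At the one-cycle levels the week 6 procedures fall after recording ends.

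**Conclusion.** The point holds as a minor one. As written, both safety outputs in 14.3 leave out AEs and SAEs judged unlikely or unrelated, so they cannot show a dose trend among such events. This matters because safety and tolerability is the primary objective, there is no concurrent control, and causality is the investigator's call.

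The size is unknown and may be negligible. The threshold for counting as related is low, since 'possible' qualifies, and no data are lost. The illustration runs from almost no difference to a clear one, depending wholly on an assumed share, and should not be read as an estimate. The conclusion rests on the text of 14.3 and on reading section 10.1 as not clearly extending to unrelated events. The 'serious' wording conflicts with section 6.1 but has little practical effect.

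**What to change.** Amend section 14.3 as follows:

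- Tabulate maximum grade by category and dose level for all AEs regardless of attribution, with related AEs shown as a subset.
- List, patient by patient, all SAEs as defined in section 6.1 regardless of attribution, together with AEs of Grade 3 or higher.
- As a terminology correction, replace 'Serious (≥ Grade 3)' with 'Severe (≥ Grade 3)'.

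The cost is a wording change, one extra table and one listing, all from data already on the CRF. No new data, visits or patients are needed, and the DLT definition and MTD rule stay as they are.
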